### Participants

Women will be mainly recruited in the middle Italy area of Bologna and Rome (Italy) and study’s materials and sensitive data will be crepitated and archived in the Department of Biomedical and Neuromotor Sciences, University of Bologna (Italy). Different recruitment procedures will be used. Firstly, informative flyers will be distributed to women contacting public services for care through collaboration with the Unit of Obstetrics and Gynaecology of the S. Orsola Hospital in Bologna. Women assessed for the first ultrasound check will be invited to participate. Secondly, informative flyers will be distributed to private gynaecologists, personal contacts of the research group, and pharmacies. The flyer will contain a summary of the study, the contacts of the researchers and a QR-code to a website created for the study (www.studiomothers.it). The website will contain further detailed information on the study rationale, aim and procedure. Interested women will be given the possibility to fill a contact form in the website; they will then be asked for their e-mail or telephone number to be contacted for the first appointment with the researcher for the screening procedure (see below in “Procedure”).

Women will be continuously recruited for circa 8 months, starting May 2024, until reaching the required sample size of 150 (see power analysis below).

Inclusion criteria will be:

age ≥ 18 yrs. old;≤ 15th week of pregnancy at the time of recruitment;good knowledge of Italian language;no severe diagnosis of relevant somatic or mental disorder (ascertained with clinical interview);no smoking;no alcohol intake;no assumption of illegal drugs;BMI ranging 18–30 (i.e., not presenting obesity or underweight following international criteria; WHO).

During the trial, participants will have no restriction to their usual care (e.g., scheduled prenatal health appointments). They will be allowed to receive concomitant care for other mental health problems (not insomnia) after enrolment.

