### Screening

Following our recruitment strategy, all women at the first ultrasound check or all women expressing interest through the study’s website will be contacted for an appointment with a clinical psychologist for the screening, which will be conducted in a confidential space in a room at the Universities’ Department involved (Department of Biomedical and Neuromotor Sciences, University of Bologna; Department of Human Sciences, Guglielmo Marconi University of Rome). This space will be used for all in-person contact with the participants (detailed below). Study’s materials, including biological samples, will all be conserved labelled with pseudonymized codes (number and letters without personal information) in a secured room in the Department of Biomedical and Neuromotor Sciences, University of Bologna for the duration of the study. A member of the research team will explain study aims and procedure. All women will be asked to read and sign the informed consent before proceeding. A separate informed consent will be asked for the use of salivary samples for the analyses of cortisol level and DNA-methylation (see “Baseline” section). Screening will be evaluated through a psychological structured interview (Structured Clinical Interview for DSM-5, SCID-5 in the brief version QuickSCID-5) [37] and a specific interview about their sleep [38] by clinical psychologists ([name], [name], [name]). Information on pregnancy and socioeconomic variables will be collected. Women will be asked to share along with their consent, gynaecological medical data on their health status (e.g. information on pregnancy).

Eligible participants will be divided in two groups:*Group A*: control group of healthy pregnant women with no insomnia complaints (*N* = 38);*Group B*: pregnant women complaining of subthreshold or clinical insomnia (*N* = 76).

Insomnia categories (absence of insomnia; subthreshold insomnia; clinical insomnia) will be operationalized using the validated questionnaire ‘Insomnia Severity Index’ (ISI) [39]. ISI is a measure of insomnia severity in the 2 weeks before compilation. Participants provide answers on a five-point Likert scale on 7 items. The score is the simple sum of the answers to all the questions and can range from 0 to 28. The total score is interpreted as follows: no insomnia (0–7); subthreshold insomnia [8–14]; clinical insomnia [15–28].

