### Randomization

Participants in Group B will be randomly assigned to one of the following two subgroups:

*Subgroup B1* (active control): psychological placebo (*N* = 38);

*Subgroup B2* (intervention): psychoeducation based on CBT-I adapted to pregnancy (*N* = 38).

Allocation concealment will be performed in steps: firstly, a code has to be created for each future participants to set the online platform they will use. The alphanumeric code (here referred to as “ID-code”) is composed of a string of numbers and the subgroup (B1 or B2). The ID-codes will be created before the start of the study by a computerized generator of random numbers. Each participant, upon allocation, will receive a folder with their ID-code, together with the instruments and information for the baseline phase (see below). A member of the research team who will not conduct screening and assignment to groups will prepare the sealed folders containing the ID-codes. The folders of Group B will be shuffled and then sequentially numbered. After the screening, each participant entering the study in the Group B will be given a numbered folder labelled with the letter “B”. With this procedure, participants will be randomly assigned to subgroup B1 or B2, concealing allocation to both participants and the investigator. Neither the psychologists conducting the screening interviews, nor the participants will know the allocation until after the screening.

Participants in the passive control condition (*Group A*) will also receive a randomly generated ID-code.

Participants will be given the credentials to log-in to their personal area on the website of the study for the next phases. The credentials will match the ID-code and thus each condition will have access to the respective online contents. The ID-codes will be used for each subsequent phase of the study.

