### Intervention

*Group A* (ISI score under 8) will be observed longitudinally through standard of care above-described procedure, without an active intervention. *Group B* (ISI score above 7) will be randomly assigned to 2 active interventions both conducted through digital therapy: (1) psychoeducation based on CBT-I adapted for pregnancy (experimental intervention; subgroup B2); (2) information on sleep disorders and on peripartum-related issues (placebo intervention; subgroup B1).

Each intervention will share the following characteristics:

fully digitalized on the study website;composed of 6 weekly 20-minutes online sessions;each session will include a before and after brief survey to monitor satisfaction;each participant will start the intervention upon completion of the baseline assessment;participants will be asked to fill out directly on the website a reduced version of the sleep and emotion diaries each day during the intervention (6 weeks).

For Group B1 (placebo), each session will include: educational videos (ca. 20 min) on aspects related to pregnancy and sleep; brief feedback questions. Participants in the placebo intervention will not be given specific indications on skills or techniques for sleep difficulties and will not have access to the weekly chat with the clinician.

Sessions will cover the following contents:

Session 1: phases of pregnancy;Session 2: sleep disorders;Session 3: nutrition and physical activity during pregnancy;Session 4: childbirth;Session 5: psychophysical development of the child in the first year of life;Session 6: synthesis of previous sessions.

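### Group B allocation order comes from an unstratified folder shuffle, which leaves avoidable chance imbalance in ISI category and site at 38 per arm

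*Protocol article*

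**What the plan says.** Under Randomization, the article builds the allocation in steps. Each participant code carries a number string and the subgroup label, and "The ID-codes will be created before the start of the study by a computerized generator of random numbers". A team member who neither screens nor assigns seals the codes in folders. Then "The folders of Group B will be shuffled and then sequentially numbered". Finally, "After the screening, each participant entering the study in the Group B will be given a numbered folder". The arms are given as 38 (B1) and 38 (B2), and Study design states a 1:1 ratio. The computer makes the codes; as described, the shuffle sets the order in which the arms are given out. No blocking, stratification, minimisation or separate set of folders per site is mentioned.

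Under Screening, the interviews and all later in-person contact take place at two departments: "Department of Biomedical and Neuromotor Sciences, University of Bologna; Department of Human Sciences, Guglielmo Marconi University of Rome". Group B is defined there as "pregnant women complaining of subthreshold or clinical insomnia", with ISI bands of 8–14 and 15–28. The Intervention section confirms that an ISI above 7 puts a woman in Group B. Primary outcomes lists the ISI total score, measured at baseline and at every follow-up. Under Statistical analysis, the factors named for the mixed model are group and time.

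**The concern.** Two baseline factors are in hand when the folder is given out: the screening site and the ISI category. The second is the banded starting value of a primary outcome, so it should be strongly prognostic for that outcome, although the article gives no correlation. Neither factor is used to balance the arms. With only 38 women per arm, one arm can easily receive visibly more women with clinical insomnia, or more women from one city.

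Two things are at stake. One is precision in the B2–B1 contrast. The other is credibility: the article plans to compare the randomised groups at baseline, and a visible difference in insomnia severity in an insomnia trial invites doubt about any result. Folders that carry instruments and are handed over in person in two cities also need a rule for which site uses which numbers, and the described procedure does not show one.

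**Working it through.** **The plan's own figures.** Total sample: 38 (A) + 38 (B1) + 38 (B2) = 114. Inflated for 24% dropout: 114 / (1 − 0.24) = 150, as the Sample size section states. The 114 itself cannot be recomputed, because the article gives neither an effect size nor a standard deviation.

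**Inputs.** From the article: N = 76 randomised women, n = 38 per arm, one unstratified shuffle. Assumed, because the article does not give them: the share of Group B with clinical insomnia, or from the smaller site, taken as 20% to 50%; and the standard deviation (SD) of baseline ISI within Group B, taken as 3 to 5 points.

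**Binary factor.** If K of the 76 women have the factor, the number X falling in one arm is hypergeometric (76, K, 38). The difference between arms in percentage points is 100 × |2X − K| / 38, with standard deviation 100 × (2/38) × √[38 × (K/76) × (1 − K/76) × 38/75]. A 15-point difference is 0.15 × 38 = 5.7 women and a 20-point difference is 7.6 women, so the first split that reaches each is as shown.

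| Assumed share | K | SD of difference | 15 points or more | 20 points or more |
|---|---|---|---|---|
| 20% | 15 | 9.2 points | 11:4 or worse, 8.2% | 12:3 or worse, 1.9% |
| 30% | 23 | 10.6 points | 15:8 or worse, 13.3% | 16:7 or worse, 4.5% |
| 40% | 30 | 11.3 points | 18:12 or worse, 24.0% | 19:11 or worse, 10.0% |
| 50% | 38 | 11.5 points | 22:16 or worse, 25.1% | 23:15 or worse, 10.8% |

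**Either factor.** Taking site and ISI category as independent, the chance that at least one differs by 15 points or more is 1 − (1 − p)². This gives 16% (both at 20%), 25% (both at 30%) and 44% (both at 50%).

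**Larger sample.** If all 150 are recruited and two thirds are in Group B, there are 100 women, 50 per arm. The same calculation gives 8% to 16% for 15 points or more and 2% to 7% for 20 points or more.

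**Mean baseline ISI.** The standard error of the arm difference is SD × √(2/38), which is 0.69, 0.92 and 1.15 for SDs of 3, 4 and 5. By the normal approximation, the arm means differ by 1 point or more in 15%, 28% and 38% of trials, and by 2 points or more in 0.4%, 3% and 8%.

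**Cost when the model adjusts for the factor.** Chance imbalance D in a factor with share P inflates the variance of the adjusted treatment effect by about 1 / (1 − r²), with r² = D² × 0.25 / [P(1 − P)]. For an 18:12 split, D = 6/38 = 0.158 and P = 30/76 = 0.395. Then r² = 0.0249 × 0.25 / 0.239 = 0.026, and the inflation is 1.027. For 19:11, D = 8/38 = 0.211, r² = 0.046 and the inflation is 1.049.

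**With stratified blocks.** In 10,000 simulated trials of 76 women for each of two settings (both factors at 30%, both at 50%), with permuted blocks of 4 within site by ISI category, none reached a 10-point difference in either factor. The largest was about 9 points. Total arm sizes differed by 4 or more in about 8% of runs and by 6 at most.

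**The case against.** The strongest reply is that nothing here is an error. Sealed folders prepared by someone who does not screen, put in random order and handed over after screening, form a sound procedure. Unstratified randomisation is unbiased and keeps the type I error, and the test already allows for chance imbalance. That stands in full; a reader who infers a biased or invalid allocation goes too far.

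Second, the design already handles part of the problem. ISI, EPDS and GAD-7 are measured at baseline and the mixed model includes the pre-treatment time point. An analysis plan that is not shown may add baseline ISI and site. This also stands. Once the model adjusts, the variance cost of the moderate splits worked above is only about 3% to 5%. It does not remove the visible imbalance or supply a per-site sequence.

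Four stronger readings are tempting, and the article does not support them.
- That the shuffle cannot be audited. Every folder has a sequential number and a code containing its arm, so a record can be kept, and nothing says that it is not. A shuffle cannot be regenerated from a seed, which is a lesser point.
- That the 1:1 ratio is materially at risk. The article does not say how many folders are prepared. If 100 were shuffled and 76 used, an assumed case, the arms would differ by 8 or more with a chance of 10%. Yet 42:34 keeps 4 × 42 × 34 / 76² = 98.9% of the efficiency of 38:38.
- That city bears directly on ISI, EPDS and GAD-7. Both interventions run on one website and the questionnaires are filled in online; no site effect is shown.
- That the shuffle is certainly manual and of one stack for both cities. The article does not say so; these are natural readings only.

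**Conclusion.** The point holds as a design improvement that is worth making, and not as a flaw that threatens validity. As described, the order of allocation ignores a prognostic category and a site that are both known at the moment of allocation. At 38 per arm, a 15-point imbalance in a given factor has a chance of roughly one in twelve to one in four, and a 20-point imbalance roughly one in fifty to one in nine. The ISI category carries most of the argument because it is the banded baseline of a primary outcome. Site is a secondary, practical reason.

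The size rests on assumed shares of 20% to 50%, on an assumed ISI standard deviation of 3 to 5 points and, for the either-factor figure, on independence of site and ISI category. The harm is lost precision and weaker face validity, and baseline adjustment recovers much of the precision.

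**What to change.** Replace the shuffle with a computer-generated 1:1 permuted-block list with varied block sizes, held by the team member who already prepares the folders and does not screen. Stratify by ISI category at screening (8–14, 15–28) and by site, and fill one numbered folder stack per stratum, so that each city has its own sequence. State in the plan that the B2–B1 model includes baseline ISI and site.

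The article gives May 2024 as the start of recruitment and was published on 10 June 2024, so some folders may already be out. In that case apply the list to the folders not yet issued and document the change, or at least adjust for baseline ISI and site.

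The cost is a short programming task and four stacks in place of one. There are two downsides. Incomplete blocks can leave a small difference in arm size (about 8% of simulated runs reached 4 or more with blocks of 4). Blocks within small strata can also make assignments guessable if staff learn earlier ones, so block sizes must be varied and concealed from those who screen and hand out folders.

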### Blinding

The screening procedure, including the clinical interviews, will be conducted before group allocation. Members of the research team scoring actigraphic data and analysing salivary samples will be blinded to participants’ allocation. Statistical analysis will be conducted on participants’ data associated with the random number labelled with the ID-code without the letter identifying the group allocation.

### Procedure

The study includes a screening phase for ascertainment of eligibility criteria and 6 phases (one baseline and 5 follow-ups).

All women will be observed longitudinally in 6 assessment evaluations (see Fig. 1):

**Fig. 1 Fig1:**

Study timeline. Legend: Circles indicate prepartum assessments; triangles indicate postpartum assessment. EMA = Ecological Momentary Assessment

Baseline: between 11th and 15th pregnant week;Follow-up-1: after 6 weeks from baseline;Follow-up-2: after 12 weeks from baseline;Follow-up-3: 1-to-2-week after birth;Follow-up-4: 3-months post-partum;Follow-up-5: 6-monhts post-partum.

For women who will be offered clinical treatment (*Group B*), baseline and follow-up-1 assessments will be conducted pre- and post-treatment (right after the 6 weeks of intervention). Partner of each participant women will be also invited to take part in the study. Their participation will include filling out online questionnaires and sleep diaries for each assessment point detailed above. At each time point of the study, participants’ will be contacted via e-mail for a reminder to log-in to their personal area of the website and complete assigned instruments and/or schedule an appointment with a member of the research team to receive the material for the observational week (see “EMA week”). The procedure is synthetized in Fig. 2.

**Fig. 2 Fig2:**
[figure not shown]
Study procedure

The full procedure of the trial will be monitored by the study coordinator [name]. Weekly appointments will be held between the coordinator and the primary investigators to review recruitment, randomization, data collection, and data analysis.

### Baseline

All participants will be asked to log-in to the study website using their personal credentials and to fill in a set of questionnaires (described in “Instruments”). Participants’ sleep and emotional processes will be monitored for 7-days through an ecological-momentary-assessment (EMA) design, which allows repeated experience sampling [40]. The EMA week will include: sleep and emotions diaries (in the morning and evening) to be completed on the website; an actigraphic (wearable wrist device) monitoring sleep-wake variables for 7 days. Under express and separate consents, on the first day of the EMA week, women will be trained to collect, at their home, saliva sample through the saliva swabs they received in their folder. Collection will be carried on in 2 time-points during the day: immediately after awakening and just before bedtime. The saliva sample will be used for evaluation of cortisol levels and for the analysis of DNA methylation of genes involved in the stress response: the FKBP5, the BDNF, and the NR3C1 [41]. Rationales for these analyses are described in “Outcomes”.

Participants will store their samples at home. At the end of the EMA week, participants will be given appointment with the researchers to bring the actigraphy and the saliva samples, closed in an envelope and already marked with unique ID-code.

Participants will be explained that their partners could also take part to the study under their expressed informed consent. Women will be given an informative form directed to partners. Within 3 days from the screening, participants will be contacted via e-mail to assess if their partners are interested to participate. In case of interest, partners’ contacts will be asked. Interested partners will receive an e-mail with their unique credentials to log-in to the website and express their informed consent. In their personal area of the website they will be asked to complete, at each phase of the study, a set of questionnaires: socio-demographic variables for Baseline; the ISI for Baseline and Follow-ups 1–5, a 7-day sleep diary for Baseline and Follow-ups 1 and 5; the Parenting Stress Index (PSI) [42] at Follow-ups 3–5. Participants and partners will be matched through an ID-code and will access their respective unique personal area on the website.

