#### Secondary outcomes

Maternal post-partum stress: Parenting Stress Index (PSI) [42] total score. Assessed at follow-up 3–4.Fathers’ Insomnia symptoms: ISI total score. Assessed at baseline, follow-up 1–5.Children sleep difficulties: Brief Infant Sleep Questionnaire (BISQ) [46] total score. assessed at follow-up 3–5.

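### Partners consent, and are probably first asked, after the woman holds a folder and log-in coded B1 or B2, so which fathers enter the fathers' ISI comparison can depend on arm

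*Protocol article*

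**What the plan says.** **Allocation (protocol article, Randomization).** "Each participant, upon allocation, will receive a folder with their ID-code", together with the baseline instruments. For the insomnia group the timing is: "After the screening, each participant entering the study in the Group B will be given a numbered folder". The outer label shows only the letter B, but the ID-code inside contains the subgroup, and the website credentials match that code. Concealment is promised up to one point: "Neither the psychologists conducting the screening interviews, nor the participants will know the allocation until after the screening".

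**Partner recruitment (Baseline).** Women are told that partners may join and are given a form for them; no date is attached to this step. Then: "Within 3 days from the screening, participants will be contacted via e-mail to assess if their partners are interested to participate". If there is interest, the woman is asked for his contact details. "Interested partners will receive an e-mail with their unique credentials to log-in to the website and express their informed consent". Woman and partner are linked through an ID-code.

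**Use of the data.** The Study aims name fathers' sleep and parental stress among the things on which effectiveness is judged. Secondary outcomes list, for fathers, "Insomnia symptoms: ISI total score", at baseline and follow-ups 1 to 5. Partners also supply sleep diaries and the PSI (Baseline).

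**Safeguards.** Blinding covers actigraphy scoring, saliva analysis and the statistical analysis. It does not mention the staff who invite partners. The intention-to-treat statement in Statistical analysis covers the randomised women.

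**The concern.** Randomisation makes B1 and B2 comparable for the women who were randomised. It does the same for their partners only if the set of contributing partners is fixed before allocation, or if joining is unaffected by arm. Here the partner joins through the woman, on her report of his interest, at a time when she may already hold a code showing her arm. If the arm influences whether she brings him in or whether he agrees, and if joining is related to his sleep, then the fathers in B2 and B1 differ before any treatment has acted. Part of the observed difference in fathers' ISI would then reflect who joined. What is at stake is one secondary outcome and the other partner-reported measures. The women's own outcomes are untouched. Group A is not randomised, so the point concerns B2 against B1 only.

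**Working it through.** **1. Order of events**

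| Step | Timing in the article | Section |
|---|---|---|
| Screening interview | Before allocation | Screening, Blinding |
| Folder with B1/B2 code | After screening, upon allocation | Randomization |
| Woman told that partners may join | Undated | Baseline |
| E-mail asking about partner interest | Within 3 days from screening | Baseline |
| Partner's contact details, credentials, online consent | After that e-mail | Baseline |
| Session 1 | On completion of baseline assessment | Intervention |

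No sentence puts partner interest or consent before allocation. That the folder comes before the e-mail is an inference from two sections. Partner consent comes later than the e-mail, so consent after allocation is the better supported of the two.

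**2. The plan's own figures.** There is no figure for partners. The only sample size step that can be rebuilt is the inflation for dropout: 114 / (1 - 0.24) = 150, as stated. The point does not depend on it. The arm size used below is the stated 38 women in each of B1 and B2.

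**3. Illustration A: uptake differs between arms.** All uptake and correlation values are assumptions. Let willingness to join be normal, with correlation rho with the father's ISI in both arms. With uptake p, the joiners' mean shifts by rho × phi(z_p)/p in SD units, where phi is the standard normal density at the threshold z_p that gives uptake p. The spurious difference is

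rho × [phi(z_p1)/p1 - phi(z_p2)/p2].

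The ratio phi(z_p)/p is 0.966 at 40%, 0.798 at 50%, 0.644 at 60% and 0.497 at 70%.

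The standard error, with SD 1, is sqrt(1/n1 + 1/n2) with n = 38p. The two-sided type I error of an unadjusted comparison is 1 - Phi(1.96 - bias/SE) + Phi(-1.96 - bias/SE).

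| rho | Uptake | Bias (SD) | SE | Type I error |
|---|---|---|---|---|
| 0.2 | 50% v 60% | 0.2 × 0.154 = 0.03 | 0.31 | about 5.1% |
| 0.3 | 50% v 70% | 0.3 × 0.301 = 0.09 | 0.30 | about 6% |
| 0.5 | 50% v 70% | 0.5 × 0.301 = 0.15 | 0.30 | about 8% |
| 0.5 | 40% v 70% | 0.5 × 0.469 = 0.23 | 0.32 | about 11% |

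**4. Illustration B: equal uptake, different selection.** No treatment effect; uptake follows a logistic model in the father's standardised ISI, with slope b in one arm and 0 in the other.

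| Uptake, both arms | b = 0.25 | b = 0.5 | b = 1.0 |
|---|---|---|---|
| 60% (about 23 fathers per arm) | 0.10 SD, 6% | 0.19 SD, 10% | 0.33 SD, 22% |
| 80% (about 30 per arm) | 0.05 SD, 5% | 0.10 SD, 7% | 0.17 SD, 11% |

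Each cell gives bias and type I error. With the same uptake and the same slope in both arms, the bias is 0 and the type I error 5%. The column b = 1.0 is extreme, because it needs strong selection in one arm and none in the other.

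**5. Would an uptake comparison reveal it?** With 38 women per arm, a 20-point gap in uptake is detected with power 0.43 (50% v 70%), 0.48 (60% v 80%) or 0.41 (40% v 60%). A non-significant uptake test would not be reassuring, and Illustration B shows that bias can exist with equal uptake.

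**The case against.** The strongest reply has five parts.

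- **The order is not stated.** Women hear the study procedure at screening, and the partner information in Baseline is undated. Procedure mentions an appointment to collect the material for the observation week, so the folder could be handed over after the e-mail. This stands. A reader might infer that the article says partners are approached only after allocation; it does not, and the point must be worded as the likely reading.
- **No session content has been seen.** Sessions start after baseline, both arms are digital with six weekly sessions, and nothing says women are told what B1 and B2 mean. This stands, and it makes strong arm-dependent uptake less likely. It does not exclude it: the code shows the arm, and the inviting staff are not said to be blinded.
- **No cut-off for partner consent.** Partners complete baseline questionnaires, which ties their entry to baseline, and an exact date may be in the full protocol. I do not count its absence as a defect.
- **Analysis can help.** A reader might infer that the bias could not be removed. That goes too far. Fathers' ISI is measured at baseline, so imbalance in existing sleep can be seen and adjusted for, and the planned mixed model would have the data. Adjustment deals with selection through baseline ISI, though not through unmeasured traits.
- **The sizes are assumed.** Correct. In the 50% v 70% cases the bias is 0.3 to 0.5 standard errors.

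**Conclusion.** The point holds as a design weakness of modest size. On the most natural reading, the set of fathers is formed after the woman's allocation and through her, so the B2-B1 comparison of fathers' ISI is not fully protected by randomisation. This rests on reading Randomization and Baseline together. A bias would need two further conditions that the documents neither show nor exclude: that the arm affects partner uptake, and that uptake is related to the father's sleep. Its size cannot be derived from the documents. Under the assumptions of Illustration A it is about 0.03 to 0.23 SD, with type I error of about 5% to 11% in an unadjusted comparison; larger values need one-sided selection. A reader might infer that the trial's main conclusions are threatened. The documents do not support that, because the women's outcomes, including all primary outcomes, do not depend on partner recruitment.

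**What to change.** 1. At the in-person screening visit, after the woman's consent and before the folder is handed over, explain partner participation and record partner interest and contact details.
2. Where feasible, obtain the partner's consent and baseline ISI before the woman's arm is revealed, or at the latest before session 1.
3. Define the main partner analysis set as partners who consented by that point, and use later joiners in a sensitivity analysis only. A set of partners merely named before allocation would not be enough, since consent and baseline data could still follow it and the selection would return as missing data.
4. Adjust the fathers' ISI comparison for the father's baseline ISI.
5. Report partner uptake and partner baseline ISI by arm, without relying on a significance test of uptake, and describe the comparison as conditional on partner participation.

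The cost is small. Steps 1 and 2 reorder existing contacts; the price is a slightly smaller partner set, since some women will want to ask their partner first, or a short delay in handing over the folder. Steps 4 and 5 use data already planned and remain possible for women already enrolled.
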